### Study design

FAITH is a multi-centre, concealed RCT using minimization to determine patient allocation. We will randomly assign a minimum of 1,000 patients who have sustained a femoral neck fracture to one of two treatment groups. The first treatment group involves fixation of the fracture with multiple small diameter cancellous screws (i.e., cancellous screw group). The second treatment group involves fixation of the fracture with a single larger diameter screw with a side plate (i.e., sliding hip screw group). We hypothesize that sliding hip screws will have lower rates of re-operation (primary outcome) and higher functional outcome scores (secondary outcome) at 24 months when compared with cancellous screws. The FAITH trial is registered at ClinicalTrials.gov (Identifier NCT00761813) and has received McMaster University Research Ethics Board approval (REB#: 06–402) and approval from local ethics boards.

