The relative risk reduction was estimated to be 25% [43]. The decision to use a 25% annual event rate in the cancellous screws group for year 1 was based upon the previous literature [25,47] and compelling preliminary aggregate data (blinded to allocation) from our pilot study. Informed by the pilot study, annual mortality rates of 15% and losses to follow-up of 5% were assumed for each group. The annual event rates by group were converted into equivalent hazard rates, assuming for simplicity that the hazard rate would be approximately constant over year 1. It was calculated that approximately 58% and 63% of the group receiving cancellous screws and the group receiving sliding hip screw fixation would be event-free and available for further follow-up at the start of year 2. It was assumed that the revision rate would fall to one-third of its initial value during year 2 of follow-up (i.e., about 10% in the cancellous screws group), that the annual mortality rate would be 10%, and that there would again be 5% of patients lost to follow-up. The sample size was also increased to allow for an estimated combined 6.8% crossover rate from the assigned to the alternate treatment, based on our pilot data.

These assumptions lead to a required total sample size of 1,441 patients, who will yield an expected number of 353 outcome revisions. For convenience, the target number of patients was rounded to 1,500. Table 2 shows the study power for a sample size of 1,500 patients (750 per group) and a range of possible values for the initial revision rate and the relative risk reduction, on either side of the central assumed values. It demonstrates that with the chosen sample size of 750 per group, there will be a high likelihood of detecting a RRR of 25% or greater across the plausible range of revision surgery rates, and moderate power for slightly lower effect sizes.

**Table 2 T2:** Estimated study power for 750 patients per treatment arm (N = 1500)

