**Baseline risk**					
**(Year 1)^**	**Relative risk reduction**				
	**10%**	**15%**	**20%**	**25%**	**30%**
**20%**	15.9%	30.8%	50.5%	70.5%	**86.1%**
**25%**	19.6%	38.7%	61.6%	**81.5%**	**93.5%**
**30%**	23.6%	46.8%	71.7%	**89.3%**	**97.4%**
**35%**	28.2%	55.2%	**80.3%**	**94.5%**	**99.1%**
**40%**	33.3%	63.6%	**87.3%**	**97.5%**	**99.7%**

*Number of patients per treatment arm, alpha = 0.05.

^Year 2 risk is 1/3 that of year 1.

Bold numbers indicate statistical power range for this study.

After 589 patients completed study follow-up, event rates were obtained and used to inform power analyses for a reduced sample size of 1,000 patients. A sample size of 1,000 patients was used in order to obtain a balance between feasibility of completing recruitment within a reasonable timeline and obtaining a sample size that will support plausible hypotheses of treatment effect and baseline event rates. Based on event rates calculated from the first 589 patients who completed the study, a 15.5% annual event rate was used for year 1 and a 27.2% annual event rate was used for year 2. Based on the data from the completed patients, it was assumed that the annual mortality rate would be 11.0% (year 1) and 18.2% (year 2) and that there would be a 12.2% (year 1) and 5.9% (year 2) loss to follow-up. The sample size was again increased to allow for an estimated combined 6.8% crossover rate from the assigned to the alternative treatment. Table 3 shows the study power for a sample size of 1,000 patients (500 per treatment group) and a range of possible values for the initial revision rate and the relative risk reduction, on either side of the central assumed values. It demonstrates that with a sample size of 500 per group, there will be a likelihood of detecting a RRR of 30% or greater across the plausible range of revision surgery rates, and moderate power for slightly lower effect sizes.

**Table 3 T3:** Estimated study power for 500 patients per treatment arm (N = 1,000)

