#### *Subgroup analyses*

We plan to conduct a single subgroup analysis comparing the effects of multiple screws versus sliding hip screw in patients with undisplaced and displaced femoral neck fractures. All analyses will be adjusted for important determinants of outcome (the prognostic variables outlined in the randomization section). The analysis plan is to fit logistic regression models and include treatment by subgroup interactions to assess whether the magnitude of the treatment effect is significantly different between subgroups. The survey and population-based data from Sweden suggests that two-thirds of all included fractures will be displaced [48]. Thus, approximately 1,000 displaced fractures (500 per group) and 500 undisplaced fractures (250 per group) can be expected. The weighted risk of revision in displaced fractures is 30.2%, (95% CI = 24.1, 6.4) and 20.4% (95% CI =17.4, 23.4%) in undisplaced fractures. The power tables suggest that the study will be able to detect relative risk reductions of 30% or greater with sliding hip screw compared to multiple cancellous screws in displaced fractures (Table 4).

**Table 4 T4:** Displaced fractures: estimated study power for 500 patients per treatment arm (N = 1,000)

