**Baseline risk**						
**(Year 1)^**	**Relative risk reduction**					
	**10%**	**15%**	**20%**	**25%**	**30%**	**40%**x
**20%**	12.0%	22.1%	36.3%	53.2%	70.1%	**93.0%**
**25%**	14.5%	27.6%	45.3%	64.5%	**81.0%**	**97.5%**
**30%**	17.2%	33.5%	45.3%	74.4%	**88.9%**	**99.2%**
**35%**	20.3%	40.0%	63.2%	**82.7%**	**94.1%**	**99.8%**
**40%**	23.8%	47.0%	71.7%	**89.2%**	**97.2%**	**100.0%**

*Number of patients per treatment arm, alpha = 0.05.

^Year 2 risk is 1/3 that of year 1.

Bold numbers indicate statistical power range for this study.

Previous randomized trials in patients with displaced fractures suggest that relative risk reductions with sliding hip screw as high as 48% are plausible [22,43-45]. Similarly, in undisplaced fractures the study will have at least 80% power to detect relative risk reductions of 40% or greater with sliding hip screws (Table 5).

**Table 5 T5:** Undisplaced fractures: estimated study power for 250 patients per treatment arm (N = 500)

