**Baseline risk**						
**(Year 1)^**	**Relative risk reduction**					
	**10%**	**15%**	**20%**	**25%**	**30%**	**40%**
**20%**	8.0%	13.2%	20.6%	30.3%	42.0%	68.0%
**25%**	9.3%	16.0%	25.5%	37.8%	51.3%	79.0%
**30%**	10.7%	19.1%	31.0%	45.6%	61.4%	**87.1%**
**35%**	12.3%	22.6%	36.3%	53.7%	70.3%	**92.7%**
**40%**	14.1%	26.5%	43.3%	61.8%	78.2%	**96.3%**

*Number of patients per treatment arm, alpha = 0.05.

^Year 2 risk is 1/3 that of year 1.

Bold numbers indicate statistical power range for this study.

Previous trials suggest risk reductions greater than 50% in undisplaced fractures [42,49]. If these previous estimates are correct, the current study will have adequate power for these analyses.

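### The subgroup power statements were not updated when the target fell to 1,000, and the 80% claim for undisplaced fractures conflicts with Table 5 itself

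*Protocol article*

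**What the plan says.** The Sample size determination section first arrives at 1,441 patients and then states: "For convenience, the target number of patients was rounded to 1,500". It goes on to replace that target: "After 589 patients completed study follow-up, event rates were obtained and used to inform power analyses for a reduced sample size of 1,000 patients". The reason given is feasibility: "A sample size of 1,000 patients was used in order to obtain a balance between feasibility of completing recruitment within a reasonable timeline". The Study design section agrees with the lower figure: "We will randomly assign a minimum of 1,000 patients who have sustained a femoral neck fracture to one of two treatment groups". The revision also changes the assumed event rates, from a year-2 rate of one-third of year 1 to 15.5% in year 1 and 27.2% in year 2.

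The Subgroup analyses section plans one subgroup factor, displaced versus undisplaced, tested by a treatment-by-subgroup interaction in logistic regression. It takes two-thirds of fractures to be displaced and continues: "Thus, approximately 1,000 displaced fractures (500 per group) and 500 undisplaced fractures (250 per group) can be expected". Revision risks are given as 30.2% (displaced) and 20.4%, interval 17.4–23.4% (undisplaced). Tables 4 and 5 use 500 and 250 per arm, and both footnotes set year-2 risk at one-third of year 1.

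Three power statements follow. For displaced fractures: "The power tables suggest that the study will be able to detect relative risk reductions of 30% or greater". For undisplaced fractures: "in undisplaced fractures the study will have at least 80% power to detect relative risk reductions of 40% or greater with sliding hip screws". Then, after citing earlier trials with reductions above 50% in undisplaced fractures: "If these previous estimates are correct, the current study will have adequate power for these analyses".

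**The concern.** The subgroup numbers and tables belong to the superseded design, in both sample size and event pattern, yet they are written as what this trial will deliver. One of the three power sentences also disagrees with the table it cites, whatever the sample size. The tables give power for the treatment effect inside one subgroup, whereas the planned test asks whether that effect differs between subgroups, which usually needs far more events.

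This is the only planned subgroup analysis, on a factor that the article's surgeon survey links to implant preference. A reader who relies on the printed figures could take a non-significant within-subgroup or interaction result as better evidence of no difference than it is.

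**Working it through.** **Step 1. Expected numbers.** 1,000 + 500 = 1,500, the old target. At 1,000 patients: 1,000 × 2/3 ≈ 667 displaced (333 per arm) and 1,000 × 1/3 ≈ 333 undisplaced (167 per arm).

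**Step 2. The undisplaced sentence against Table 5 (no modelling).** The 40% RRR column, at 250 per arm, reads:

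| Baseline risk | 20% | 25% | 30% | 35% | 40% |
|---|---|---|---|---|---|
| Power | 68.0% | 79.0% | 87.1% | 92.7% | 96.3% |

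Power of 80% is reached only in the rows from 30% upwards. The stated risk is 20.4%, and even the upper limit of its interval, 23.4%, lies below the 25% row.

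**Step 3. Reproducing the tables.** Inputs from Sample size determination: mortality 15% then 10%, loss 5% in each year, crossover 6.8%, two-sided alpha 0.05. From the table footnotes: year-2 risk = year-1 risk/3. Assumed: crossover multiplies events by (1 − 0.068)² = 0.869, since the article does not give the form.

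- Hazards: h(x) = −ln(1 − x), treated as competing and constant within each year.
- Sliding hip screw risk = baseline × (1 − RRR); HR = ratio of year-1 revision hazards.
- Power = Φ[(√E/2) × |ln HR| − 1.96], with E the crossover-adjusted events.

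Table 4 at 30% risk and 30% RRR:
- Cancellous screws: year-1 hazards 0.357 + 0.163 + 0.051 = 0.571; event probability 0.272 in year 1 and 0.052 in year 2, total 0.324.
- Sliding hip screw (risk 0.21): 0.190 + 0.041 ≈ 0.231.
- Events: 500 × (0.3242 + 0.2312) ≈ 277.7; × 0.869 ≈ 241.
- HR = 0.236/0.357 = 0.661.
- Power = Φ(7.77 × 0.414 − 1.96) = Φ(1.26) = 89.6%, against 88.9% printed.

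Table 5 at 20% risk and 40% RRR gives 68.7%, against 68.0% printed. All other cells of Tables 4 and 5 agree within about 1.5 points except one: Table 4 at 30% risk and 20% RRR prints 45.3%, the value of the row above, and computes to about 55%. At 1,441 patients the method gives 346 events before the crossover factor, against 353 stated.

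**Step 4. Same method at the current size.** Two routes: rerun the model at 333 and 167 per arm, or scale the printed cell by Φ[(z + 1.96) × √(2/3) − 1.96], where z is the normal quantile of the printed power. For 88.9%: z = 1.221, and Φ(3.181 × 0.8165 − 1.96) = Φ(0.637) = 73.8%.

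| Subgroup, risk, RRR | Printed (N = 1,500) | Scaled cell | Model |
|---|---|---|---|
| Displaced, 30%, 30% | 88.9% | 73.8% | 74.7% |
| Undisplaced, 20%, 40% | 68.0% | 50.9% | 51.6% |
| Undisplaced, 20.4%, 40% | – | – | 52.5% |
| Undisplaced, 25%, 40% | 79.0% | 61.7% | 62.6% |

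For larger effects the model gives, for displaced fractures at 30.2% risk, about 95% at 40% RRR and 99% at 48%. For undisplaced fractures at 20.4% it gives about 75% at 50% RRR and 92% at 60%.

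**Step 5. Revised event rates.** The article gives no revised rates by subgroup. Assume the overall revised values in both: revision 15.5%/27.2%, mortality 11.0%/18.2%, loss 12.2%/5.9%, with the crossover factor. Displaced at 30% RRR: E ≈ 148, HR 0.682, power about 64%. Undisplaced at 40% RRR: E ≈ 70, HR 0.580, power about 63%.

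**Step 6. The planned interaction.** The planned model is logistic; this is an approximation on the log hazard ratio scale. SE = √(4/E_displaced + 4/E_undisplaced), at N = 1,000, with 30.2% and 20.4% risk. For RRR 30% versus 50%: SE = √(4/161.7 + 4/49.3) = 0.325; difference = ln(0.6606/0.4715) = 0.337; power = Φ(0.337/0.325 − 1.96) ≈ 18%.

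| RRR displaced vs undisplaced | Interaction power |
|---|---|
| 30% vs 40% | about 7% |
| 30% vs 50% | about 18% |
| 30% vs 0% | about 29% |
| 48% vs 0% | about 70% |

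**The case against.** A reader might infer that the subgroup power simply does not exist. The documents do not support that. The article regards reductions as high as 48% in displaced fractures as plausible, and effects of 40–48% keep about 95–99% power within that subgroup at 1,000 patients. The displaced sentence also agreed with Table 4 at 30% risk when the target was 1,500; its shortfall comes from the sample size alone. Apart from the one cell, the tables are arithmetically sound for the old design.

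Nor is the adequate-power sentence plainly false. It is conditional on reductions above 50% in undisplaced fractures. Within that subgroup, power is about 75% at exactly 50% and passes 80% before 60%; on the revised overall rates it is about 85% at 50%. That sentence needs limiting, not deleting. What it cannot cover is the interaction test.

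It can fairly be said that Tables 4 and 5 are labelled as within-subgroup power and are never called interaction power, and that an article need not print interaction power. That stands. The fault is that the adequacy claim refers to the planned analyses without distinguishing the two. Any single interaction figure depends on the contrast chosen, so only a range is fair.

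The target is a minimum, so some over-recruitment would raise the figures slightly, but nothing in the text still plans for 1,500. Without any crossover loss, displaced power at 30% RRR would be about 81%, but the article states that it allows for 6.8%. Prespecifying one subgroup with a formal interaction test limits the risk of misreading. None of this answers the stale numbers or the conflict with Table 5.

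**Conclusion.** The point holds in this limited form. The expected subgroup sizes and Tables 4 and 5 describe a 1,500-patient trial with a superseded event pattern. The claim of at least 80% power in undisplaced fractures is wrong as written, even at 250 per arm. At the current size, the stated thresholds are not reached:

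- Displaced, 30% RRR: about 74–75% on the tables' method, or about 64% on the revised overall rates.
- Undisplaced, 40% RRR: about 51–53% at 20–20.4% risk and about 62% at 25%, or about 63% on the revised overall rates.

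The interaction test has roughly 7% to 70% power over the contrasts tried.

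These figures rest on the assumed form of the crossover factor, on reading the stated subgroup risks as year-1 risks, and, for the revised-rate figures, on equal rates in both subgroups. If the stated risks are instead cumulative, a plain two-proportion calculation without crossover gives 76% (displaced, 30.2%, 30% RRR) and 52% (undisplaced, 20.4%, 40% RRR). The conflict between the sentence and Table 5 needs none of these assumptions.

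This should be fixed, but it concerns one secondary analysis. The primary power was recalculated for 1,000 patients in Table 3 and does not depend on this section.

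**What to change.** - Restate the expected numbers as about 667 displaced and 333 undisplaced.
- Recompute Tables 4 and 5 for about 333 and 167 per arm, stating the year-1 and year-2 rates assumed in each subgroup. The article gives revised rates only overall, so subgroup rates must be supplied or the assumption of equal rates declared.
- Replace the undisplaced 80% sentence and the displaced 30% RRR sentence with the recomputed figures.
- Limit the adequate-power sentence to within-subgroup effects large enough to reach it, and say that it does not apply to the interaction test.
- Give a range of interaction power, or label the interaction analysis exploratory.
- As a side correction, replace the 45.3% in Table 4 at 30% risk and 20% RRR, which should be about 54–55% at 500 per arm. No claim depends on that cell.

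The cost is a recalculation and a few rewritten sentences. No change to design, recruitment or data collection is needed.

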**Baseline risk**						
**(Year 1)^**	**Relative risk reduction**					
	**10%**	**15%**	**20%**	**25%**	**30%**	**40%**x
**20%**	12.0%	22.1%	36.3%	53.2%	70.1%	**93.0%**
**25%**	14.5%	27.6%	45.3%	64.5%	**81.0%**	**97.5%**
**30%**	17.2%	33.5%	45.3%	74.4%	**88.9%**	**99.2%**
**35%**	20.3%	40.0%	63.2%	**82.7%**	**94.1%**	**99.8%**
**40%**	23.8%	47.0%	71.7%	**89.2%**	**97.2%**	**100.0%**

*Number of patients per treatment arm, alpha = 0.05.

^Year 2 risk is 1/3 that of year 1.

Bold numbers indicate statistical power range for this study.

Previous randomized trials in patients with displaced fractures suggest that relative risk reductions with sliding hip screw as high as 48% are plausible [22,43-45]. Similarly, in undisplaced fractures the study will have at least 80% power to detect relative risk reductions of 40% or greater with sliding hip screws (Table 5).

**Table 5 T5:** Undisplaced fractures: estimated study power for 250 patients per treatment arm (N = 500)

**Baseline risk**						
**(Year 1)^**	**Relative risk reduction**					
	**10%**	**15%**	**20%**	**25%**	**30%**	**40%**
**20%**	8.0%	13.2%	20.6%	30.3%	42.0%	68.0%
**25%**	9.3%	16.0%	25.5%	37.8%	51.3%	79.0%
**30%**	10.7%	19.1%	31.0%	45.6%	61.4%	**87.1%**
**35%**	12.3%	22.6%	36.3%	53.7%	70.3%	**92.7%**
**40%**	14.1%	26.5%	43.3%	61.8%	78.2%	**96.3%**

*Number of patients per treatment arm, alpha = 0.05.

^Year 2 risk is 1/3 that of year 1.

Bold numbers indicate statistical power range for this study.

Previous trials suggest risk reductions greater than 50% in undisplaced fractures [42,49]. If these previous estimates are correct, the current study will have adequate power for these analyses.

#### *Interim analysis*

An interim analysis will not be conducted. The trial will not be stopped early for benefit. The Data Safety Monitoring Board (DSMB) will monitor Adverse Events (AEs) and may make recommendations to the Principal Investigators and Steering Committee to stop the study for harm only.

### Data management

The Case Report Forms (CRFs) will be the primary data collection tool for the study. All data requested on the CRF must be recorded. An Electronic Data Capture system will be used to submit data to the Methods Centre located at McMaster University. Upon receipt of the data, the personnel at the Methods Centre will make a visual check of the data and they will query all missing data, implausible data, and inconsistencies.

### Ethical considerations

All patients will be provided a consent form describing the study and providing sufficient information to make an informed decision about their participation in this study. The consent form will be submitted with the protocol for review and approval by the REB/Institutional Review Board (IRB) for the study. The formal consent of a patient, using the REB/IRB-approved consent form, must be obtained before that patient undergoes any study procedure. Any amendments to the study protocol which may affect the conduct of the study, or the potential safety of or benefits to patients will require a formal amendment to the protocol requiring approval by McMaster University’s REB and local research ethics boards for clinical sites.

Information about study patients will be kept confidential and will be managed in accordance with the following rules: (1) All study-related information will be stored securely at the clinical site; (2) All study patient information will be stored in locked file cabinets and accessible only to study personnel; (3) All CRFs will be identified only by a coded patient number and initials; (4) All records that contain patient names, or other identifying information, will be stored separately from the study records that are identified only by the coded patient number and initials; and (5) All local databases will be password protected.

### Study committees

#### *Steering committee*

The Steering Committee is comprised of orthopaedic surgeons, a statistician, and research methodologists. The Steering Committee will provide guidance and direction to the overall trial.

### Data safety and monitoring board

The DSMB is comprised of Medical Doctors, a Safety Officer, and a Statistician who remain completely independent of the study investigators. The DSMB will review accumulated safety data from the trial and advise the Principal Investigators and the Steering Committee on items related to patient safety.

### Dissemination

Results from the primary manuscript will be submitted for publication regardless of whether or not there are significant findings. Every attempt will be made to ensure that the amount of time between completion of data collection and release of study findings are minimized.

Only the Methods Centre will have access to the full trial dataset. Data for the primary publication will be analyzed exclusively by the Methods Centre. Requests for access to the full trial dataset for secondary publications are encouraged and can be initiated through a written request to Methods Centre personnel.

## Discussion

Most of the current literature evaluating the efficacy of internal fixation at treating hip fractures is focused on the comparison between internal fixation and arthroplasty, which does not allow for a direct comparison of different methods of internal fixation. The RCTs that directly evaluate different types of internal fixation have been too small to definitively guide Orthopaedic practices as they lack sufficient power to reliably detect important treatment effects and some contain important methodological limitations [16,25]. FAITH will be the largest trial to date informing the question of the impact of cancellous screws and sliding hip screws on outcomes in patients with femoral neck fractures. With over 1000 patients, FAITH will have adequate power to detect important treatment effects and will help to inform Orthopaedic practice. FAITH will include patients from North America, Europe, Asia, and Australia making results generalizable to several different geographic populations.

Our previous trial evaluating reamed versus non-reamed nailing in over 1,300 patients with tibial shaft fractures (SPRINT) set a new benchmark for the conduct of RCTs in Orthopaedic surgery [50,51]. The FAITH trial expands upon the successful methodology employed in SPRINT and will set the bar higher as we expand our collaboration worldwide and recruit a larger number of patients, while maintaining methodological rigor. Ultimately, this RCT will move Orthopaedic surgical trials one step closer to the standards of global impact RCTs that are currently conducted in cardiovascular medicine and cerebrovascular surgery (e.g. POISE Trial Investigators, 2006; PROTECT Investigators, 2011) [52,53].

Since treatment allocation is concealed there will be no risk of conscious or unconscious selection bias on the part of the researchers, as can occur when it is possible for researchers to predict treatment assignment. Further, minimization will be used to ensure prognostic balance between intervention groups for relevant patient factors. The minimization approach evaluates the marginal distribution of each prognostic variable and then sums over the variables as each patient is assigned to a treatment group. Unlike random permuted block within strata, minimization works toward minimizing the total imbalance for all factors together instead of considering mutually exclusive subgroups [26] which may be considered an additional strength.

One limitation of the FAITH trial is the inability to blind patients, surgeons, and outcome adjudicators. Patients cannot be blinded as the two devices leave unique scarring patterns and surgeons cannot be blinded as the devices are easily discernible. It was planned that outcome adjudicators would be blinded to study treatment arm by digitally superimposing cancellous screws and the sliding hip screw on the same x-ray image for the assessments of quality of fracture reduction, fracture healing, infection, and avascular necrosis. However, after piloting this approach we found that it was still possible to often correctly identify the true treatment, and that difficulties with adjudication were created because of too much bone being covered. Therefore this approach was found to be infeasible for adjudicating and as a result outcome adjudicators will not be blinded to study treatment during their assessment of patients’ radiographic characteristics and quality of surgery. However, as revision surgery (the primary outcome) is objective, it is expected that a lack of blinding will not introduce significant threats to validity. To limit the minimal risk of bias that unblinded adjudication can create, a CAC will be used and consensus will be required on all adjudication events.

There is inconclusive evidence within the literature regarding operative method of internal fixation for femoral neck fractures. Prior evidence has suggested sliding hips screws may be superior to cancellous screws, but these findings have been based on studies with small sample sizes and low events numbers [25]. Advocates of multiple cancellous screws focus upon its superior torsional stability, limited disruption of femoral head blood supply, and minimally invasive insertion, while proponents of the sliding hip screw believe its superior biomechanical properties and greater fracture stability in osteoporotic bone should decrease the need for revision surgery. Despite the evidence suggesting the superiority of sliding hip screws, 90% of surgeons preferred cancellous screws over sliding hip screws for treating undisplaced fractures and 68% preferred cancellous screws over sliding hip screws in treating displaced fractures. Definitively identifying the optimal surgical approach to the initial management of femoral neck fractures has enormous potential to improve the lives of hundreds of thousands of individuals who suffer these injuries each year. The relative simplicity and ease of application of the proposed interventions will have wide applicability where trauma burden and disability from hip fractures is high. This trial will not only change current orthopaedic practice, but will set a benchmark for the conduct of future orthopaedic trials.
